### 10.1.4. Data Protection

The study sponsor and investigators will guarantee the confidentiality of the subjects' data and ensure compliance at all times with current legislation (General Regulation of Data Protection – Reglamento General de Protección de datos (RGPD) 679/2016).

- Participants will be assigned a unique identifier by the sponsor. Any participant records or datasets that are transferred to the sponsor will contain the identifier only; participant names or any information which would make the participant identifiable will not be transferred.
- The participant must be informed that his/her personal study-related data will be used by the sponsor in accordance with local data protection law. The level of disclosure must also be explained to the participant who will be required to give consent for their data to be used as described in the informed consent

- The participant must be informed that his/her medical records may be examined by Clinical Quality Assurance auditors or other authorized personnel appointed by the sponsor, by appropriate IRB/IEC members, and by inspectors from regulatory authorities.

#### **10.1.5. Committees Structure**

##### **10.1.5.1 Early Safety Data Committee**

- Participant safety will be continuously monitored by the Sponsor's internal committee, which includes safety signal detection at any time during the study
- In addition, an early aggregated safety data review will be performed, the goal of which is to allow for a cautious, stepwise approach to drug administration. An initial safety review for this study is planned for the first 30 participants (50% of participants) who are dosed and have provided safety data for 28 days after administration of Dose 1
- All safety data collected will be summarized and reviewed by the Sponsor's internal committee for agreement of next steps.
- In particular, data will be reviewed by the Sponsor for identification of the following events that would potentially contribute to a requirement to stop the study.
  - Any deaths, regardless of causality
  - Grade 3 AEs reported in more than 2 participants (see table in Appendix 4)
- Enrollment will be paused during the review. If a stopping rule is met, a decision will be made, based on the review, as to whether enrollment in the study will be allowed to resume.
- Case unblinding may be performed for above reviews if necessary.

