#### **7.1.2. Temporary Discontinuation**

Study medication must be temporary discontinued in the following circumstances:

- Liver laboratory abnormalities: ALT over 5 times the upper limit of normal (ULN) or ALT over 3xULN and bilirubin over 1.5xULN or any verified Grade 4 laboratory abnormality that to the investigators criteria would affect the safety of the participant.

- Acute disorders that involve a risk of impaired kidney function such as dehydration, severe infection, or shock.
- Acute or chronic disease capable of causing tissue hypoxia, such as heart or respiratory failure, recent myocardial infarction, shock, or stroke.
- Hepatic failure, acute alcohol intoxication, alcoholism.
- Study medication should be stopped at the time of surgical intervention with general, spinal, or epidural anesthesia. Treatment can be restarted 48 hours after the intervention surgical procedure or after resumption of oral feeding, provided renal function has been reassessed and proven to be stable.
- Study medication should be stopped prior to or at the time of intravenous iodinated contrast test and should not be restarted until at least 48 hours, provided kidney function has been reassessed.
- Participants unable to swallow study medication tablets during the treatment period.
- Participants starting other temporary medications that according to study drug label are contraindicated with metformin. (Appendix 7)
- Any new events, comorbidities or medications that according to the investigator could entail additional risks for the participant.

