#### 10.4.2. Definition of SAE

**An SAE is defined as any serious adverse event that, at any dose:**

**a. Results in death**

**b. Is life-threatening**

The term 'life-threatening' in the definition of 'serious' refers to an event in which the participant was at risk of death at the time of the event. It does not refer to an event, which hypothetically might have caused death, if it were more severe.

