### **Assessment of Intensity**

The investigator will make an assessment of intensity for each AE and SAE reported during the study

- The intensity of the AE will be graded following the DAIDS grading table for Severity of AEs.(43)
- AE severity grading scale ranging from grades 1 to 5 with descriptions for each AE based on the following general guidelines:
  - Grade 1 indicates a mild event (An event that is easily tolerated by the participant, causing minimal discomfort and not interfering with everyday activities)
  - Grade 2 indicates a moderate event (An event that causes sufficient discomfort to interfere with normal everyday activities.)
  - Grade 3 indicates a severe event (An event that prevents normal everyday activities. An AE that is assessed as severe should not be confused with an SAE. Severe is a category utilized for rating the intensity of an event; and both AEs and SAEs can be assessed as severe.

An event is defined as ‘serious’ when it meets at least 1 of the predefined outcomes as described in the definition of an SAE, NOT when it is rated as severe.

  - Grade 4 indicates a potentially life-threatening event
  - Grade 5 indicates death
- If the severity of an AE could fall in either one of two grades (i.e., the severity of an AE could be either grade 2 or grade 3), sites should select the higher of the two grades.

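### The early safety review's severe-AE criterion names Grade 3 only, so on its literal wording non-fatal Grade 4 AEs do not count towards it

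*Protocol*

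**What the plan says.** Section 10.1.5.1 (Early Safety Data Committee) plans an aggregated safety review of the first 30 participants, stated as 50% of the total, once they have 28 days of safety data after the first dose. The sponsor's internal committee looks for the "following events that would potentially contribute to a requirement to stop the study". Two are listed. One is any death, whatever its cause. The other is "Grade 3 AEs reported in more than 2 participants (see table in Appendix 4"). Enrolment is paused during the review. The section then treats the list as a stopping rule: "If a stopping rule is met, a decision will be made, based on the review", on whether enrolment resumes.

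The table reference leads to the intensity grading in Appendix 4 (Section 10.4.3), an "AE severity grading scale ranging from grades 1 to 5". Grade 3 is a severe event, "Grade 4 indicates a potentially life-threatening event", and Grade 5 is death. No other section adds 'or higher' to the criterion or sets a study-level trigger for Grade 4.

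**The concern.** The two listed events cover Grade 5 (through deaths) and Grade 3 (through the count). Non-fatal Grade 4 lies between them and, as worded, is in neither. The severity order is therefore inverted: a set of severe events meets the criterion, and the same number of potentially life-threatening events does not.

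The written threshold is what the committee, an ethics committee or an inspector would check against. It cites a table that separates the grades, so it should not depend on the reader supplying the missing words.

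**Working it through.** **Inputs from the protocol**
- Review size: 30 participants (Section 10.1.5.1).
- Planned total: 30 per group in two groups (Section 9.2).
- Criterion: Grade 3 AEs in more than 2 participants, that is, in at least 3.
- Grades 3, 4 and 5 are separate categories, one per event (Appendix 4).

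**The plan's own figure.** 30 / (2 × 30) = 30/60 = 50%, as stated. The threshold is 3/30 = 10% of those reviewed.

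**The wording applied to simple cases (no assumptions needed)**

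| Among the 30 reviewed | Criterion as written | With 'or higher' added |
|---|---|---|
| 3 with a Grade 3 AE | met | met |
| 3 with only non-fatal Grade 4 AEs | not met | met |
| 2 with a Grade 3 AE, 1 with only non-fatal Grade 4 | not met | met |
| 2 with a Grade 3 AE, 28 (= 30 − 2) with only non-fatal Grade 4 | not met | met |

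The last row is a logical limit, not a realistic scenario. A participant with both a Grade 3 and a Grade 4 AE counts under either wording.

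**Illustration under assumed rates.** The protocol gives no AE rates, so these values are assumptions. Let p3 be the chance that a participant has at least one Grade 3 AE by the review, and p4 the chance of a Grade 4 AE without any Grade 3 AE. Participants are taken as independent. The chance of meeting the criterion is

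P(X ≥ 3) = 1 − Σ (k = 0 to 2) C(30, k) p^k (1 − p)^(30 − k),

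with p = p3 for the literal wording and p = p3 + p4 for Grade 3 or higher. For p = 0.05 the three terms are 0.2146, 0.3389 and 0.2586, so P = 1 − 0.812 = 0.188.

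| p3 | As written | Grade 3 or higher, p4 = 1% | Grade 3 or higher, p4 = 2% |
|---|---|---|---|
| 2% | 2.2% | 6.0% | 11.7% |
| 5% | 18.8% | 26.8% | 35.1% |
| 8% | 43.5% | 51.4% | 58.9% |

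The smallest difference is 6.0 − 2.2 = 3.8 percentage points and the largest is 35.1 − 18.8 = 16.3. These figures show how often a non-binding flag would be raised. They do not measure participant risk, and the textual point does not depend on them.

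**The case against.** The strongest reply is that the criterion changes little in operation. The list is introduced as particular examples, its events only potentially contribute to stopping, and a met rule leads to a decision rather than to automatic termination. Enrolment is paused and all safety data are reviewed whether or not a criterion is met. The committee also monitors continuously and can detect a signal at any time. All of this stands. A reader might infer that the trial could run on unchecked through a cluster of Grade 4 events; the documents do not support that.

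Other safeguards cover part of the gap:
- **SAE reporting.** A Grade 4 AE is not automatically an SAE. The life-threatening criterion is limited to events with actual risk of death at the time: "It does not refer to an event, which hypothetically might have caused death, if it were more severe". However, criterion f in Section 10.4.2 says that significant medical events that may jeopardise the participant, or that need intervention to prevent a serious outcome, should usually be considered serious. Many Grade 4 events would plausibly qualify, and SAEs reach the sponsor within 24 hours (Section 8.5.1).
- **Section 7.1.2.** Study drug is interrupted for "any verified Grade 4 laboratory abnormality that to the investigators criteria would affect the safety of the participant". This applies to one participant at a time and to laboratory findings only.

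Neither safeguard supplies or corrects the numeric threshold.

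A reader might also infer that the Appendix 4 instruction for borderline events, that "sites should select the higher of the two grades", weakens the threshold by moving Grade 3/4 events out of the count. The documents do not support a net weakening. The same instruction moves Grade 2/3 events into the count, and that is the only example the appendix gives.

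Finally, the intended meaning was probably Grade 3 or higher. If so, writing it down changes nothing that the sponsor planned.

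**Conclusion.** The point holds as a minor correction of a stated decision threshold. On the literal wording, non-fatal Grade 4 AEs do not count towards the severe-AE criterion, so three participants with only such events miss a threshold that three with Grade 3 AEs meet. This follows from Section 10.1.5.1 and the Appendix 4 scale alone. The practical effect is limited by the general review, the committee's continuous monitoring and discretion, SAE reporting and Section 7.1.2. The range of 3.8 to 16.3 percentage points is an illustration that rests wholly on assumed rates and on independence between participants.

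**What to change.** In the second listed event of Section 10.1.5.1, insert the words 'or higher' after 'Grade 3'. Keep the threshold of more than 2 participants, the reference to Appendix 4, the timing of the review and the rest of the section.

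The change needs no new visits, samples or analyses. The criterion may be met somewhat more often. Because enrolment is already paused during the review, meeting it only leads to the decision on resuming enrolment that the section already provides for.

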#### **10.1.6. Dissemination of Clinical Study Data**

Study information from this protocol will be posted on publicly available clinical trial registers before enrollment of subjects begins.

#### **10.1.7. Data Quality Assurance**

- All participant data relating to the study will be recorded on printed or electronic CRF unless transmitted to the sponsor or designee electronically (e.g., laboratory data). The investigator is responsible for verifying that data entries are accurate and correct by physically or electronically signing the CRF.
- Guidance on completion of CRFs will be provided in the Trial Master File.
- The investigator must permit study-related monitoring, audits, IRB/IEC review, and regulatory agency inspections and provide direct access to source data documents.

- Monitoring details describing strategy, including definition of study critical data items and processes (eg, risk-based initiatives in operations and quality such as risk management and mitigation strategies and analytical risk-based monitoring), methods, responsibilities, and requirements, including handling of noncompliance issues and monitoring techniques (central, remote, or on-site monitoring) are provided in the monitoring plan.
- Monitoring details describing strategy (e.g., risk-based initiatives in operations and quality such as Risk Management and Mitigation Strategies and Analytical Risk-Based Monitoring), methods, responsibilities and requirements, including handling of noncompliance issues and monitoring techniques (central, remote, or on-site monitoring) are provided in the Monitoring Plan.
- The sponsor or designee is responsible for the data management of this study including quality checking of the data.
- The sponsor assumes accountability for actions delegated to other individuals (e.g., Contract Research Organizations).
- Records and documents, including signed ICFs, pertaining to the conduct of this study must be retained by the investigator for 10 years after study completion unless local regulations or institutional policies require a longer retention period. No records may be destroyed during the retention period without the written approval of the sponsor. No records may be transferred to another location or party without written notification to the sponsor.

#### **10.1.8. Source Documents**

- Source documents provide evidence for the existence of the participant and substantiate the integrity of the data collected. Source documents are filed at the investigator's site.
- Data reported on the CRF or entered in the eCRF that are transcribed from source documents must be consistent with the source documents or the discrepancies must be explained. The investigator may need to request previous medical records or transfer records, depending on the study. Also, current medical records must be available.
- The investigator must maintain accurate documentation (source data) that supports the information entered in the CRF.
- Study monitors will perform ongoing source data verification to confirm that data entered into the CRF by authorized site personnel are accurate, complete, and verifiable from source documents; that the safety and rights of participants are being protected; and that the study is being conducted in accordance with the currently approved protocol and any other study agreements, ICH GCP, and all applicable regulatory requirements.

### **10.1.9. Study and Site Start and Closure**

#### **First Act of Recruitment**

The study start date is the date on which the clinical study will be open for recruitment of participants.

#### **Study/Site Termination**

The sponsor or designee reserves the right to close the study site or terminate the study at any time for any reason at the sole discretion of the sponsor. Study sites will be closed upon study completion. A study site is considered closed when all required documents and study supplies have been collected and a study-site closure visit has been performed.

The investigator may initiate study-site closure at any time, provided there is reasonable cause and sufficient notice is given in advance of the intended termination.

Reasons for the early closure of a study site by the sponsor or investigator may include but are not limited to:

For study termination:

- Discontinuation of further study intervention development

For site termination:

- Failure of the investigator to comply with the protocol, the requirements of the IRB/IEC or local health authorities, the sponsor's procedures, or GCP guidelines
- Inadequate or no recruitment (evaluated after a reasonable amount of time) of participants by the investigator
- Total number of participants included earlier than expected

If the study is prematurely terminated or suspended, the sponsor shall promptly inform the investigators, the IECs/IRBs, the regulatory authorities, and any contract research organization(s) used in the study of the reason for termination or suspension, as specified by the applicable regulatory requirements. The investigator shall promptly inform the participant and should assure appropriate participant therapy and/or follow-up

### **10.1.10. Publication Policy**

- The results of this study may be published or presented at scientific meetings. If this is foreseen, the investigator agrees to submit all manuscripts or abstracts to the sponsor before submission. This allows the sponsor to protect proprietary information and to provide comments.
- The sponsor will comply with the requirements for publication of study results. In accordance with standard editorial and ethical practice, the sponsor will generally support

publication of multicenter studies only in their entirety and not as individual site data. In this case, a coordinating investigator will be designated by mutual agreement.

- Authorship will be determined by mutual agreement and in line with International Committee of Medical Journal Editors authorship requirements.

## 10.2. Appendix 2: Clinical Laboratory Tests

- The tests detailed in Table 2 will be performed by the local laboratory at La Paz University Hospital.
- The tests detailed in Table 3 will be performed by the local laboratory at IdiPaz.
- Table 4 specifies the collection tubes for each visit.
- Protocol-specific requirements for inclusion or exclusion of participants are detailed in Section 5 of the protocol.
- Investigators must document their review of each laboratory safety report.
- Additional tests may be performed at any time during the study as determined necessary by the investigator or required by local regulations.

**Table 2: Protocol-Required Safety Laboratory Tests**

| Laboratory Tests                | Parameters                                                                                                                                                                                                                                        |                                               |                                   |                                                                                                                        |
|---------------------------------|---------------------------------------------------------------------------------------------------------------------------------------------------------------------------------------------------------------------------------------------------|-----------------------------------------------|-----------------------------------|------------------------------------------------------------------------------------------------------------------------|
| Hematology                      | Platelet Count                                                                                                                                                                                                                                    | RBC Indices:
MCV
MCH
% Reticulocytes |                                   | White blood cell (WBC) count with Differential:
Neutrophils
Lymphocytes
Monocytes
Eosinophils
Basophils |
|                                 | Red blood cell (RBC) Count                                                                                                                                                                                                                        |                                               |                                   |                                                                                                                        |
|                                 | Hemoglobin                                                                                                                                                                                                                                        |                                               |                                   |                                                                                                                        |
|                                 | Hematocrit                                                                                                                                                                                                                                        |                                               |                                   |                                                                                                                        |
|                                 | CD4 + and CD8 + cell count                                                                                                                                                                                                  |                                               |                                   |                                                                                                                        |
| Clinical Chemistry  | Blood urea nitrogen (BUN)                                                                                                                                                                                                                         | Potassium                                     | Aspartate Aminotransferase (AST)  | Total and direct bilirubin                                                                                             |
|                                 | Creatinine                                                                                                                                                                                                                                        | Sodium                                        | Alanine Aminotransferase (ALT)    | Total Protein Albumine                                                                                                 |
|                                 | Fasting Glucose                                                                                                                                                                                                                                   | Calcium                                       | Alkaline phosphatase  | Vitamin D                                                                                                              |
| Routine Urinalysis              | 

Specific gravity

pH, glucose, protein, blood, ketones, bilirubin, urobilinogen, nitrite, leukocyte esterase by dipstick

Microscopic examination (if blood or protein is abnormal)

 |                                               |                                   |                                                                                                                        |
| Other Screening Tests           | 

Serology: hepatitis B surface antigen (HBsAg), and hepatitis C virus antibody (or RNA test in the case of a previous positive antibody test)

HIV-1 Viral load.

                            |                                               |                                   |                                                                                                                        |

|                                                                                                                                                                                                                                                                                                                                                                                                                                                                                                                                                                                                                                                                                                                                                                                                                                                                                                                                                                                                                                  |                                                                                                                                                                                                                                            |
|----------------------------------------------------------------------------------------------------------------------------------------------------------------------------------------------------------------------------------------------------------------------------------------------------------------------------------------------------------------------------------------------------------------------------------------------------------------------------------------------------------------------------------------------------------------------------------------------------------------------------------------------------------------------------------------------------------------------------------------------------------------------------------------------------------------------------------------------------------------------------------------------------------------------------------------------------------------------------------------------------------------------------------|--------------------------------------------------------------------------------------------------------------------------------------------------------------------------------------------------------------------------------------------|
|                                                                                                                                                                                                                                                                                                                                                                                                                                                                                                                                                                                                                                                                                                                                                                                                                                                                                                                                                                                                                                  | 
 
• B12 vitamin levels.
 
• Glycated hemoglobin (A1C).
 
• IGF-1
 
• Fasting insulin
 
• HOMA-IR
 
• D-dimer
 
• Cystatin C
 
• NT-proBNP
 
 |
| 
NOTES:
 
 Details of liver chemistry stopping criteria and required actions and follow-up are given in Section [7.1.1 Liver Chemistry Stopping Criteria] and Appendix [6: Liver Safety: Suggested Actions and Follow-up Assessments [and Study Intervention Rechallenge Guidelines]]. All events of ALT [or AST] <math>\geq 3 \times</math> upper limit of normal (ULN) and total bilirubin <math>\geq 2 \times</math> ULN (<math>>35\%</math> direct bilirubin) or ALT [or AST] <math>\geq 3 \times</math> ULN and international normalized ratio (INR) <math>>1.5</math>, (if INR measured) which may indicate severe liver injury (possible Hy's Law), must be reported to [sponsor] in an expedited manner (excluding studies of hepatic impairment or cirrhosis).
 
 If alkaline phosphatase is elevated, consider fractionating.
 
 Local urine testing will be standard for the protocol unless serum testing is required by local regulation or IRB/IEC.
 |                                                                                                                                                                                                                                            |

